#### Neuromuscular block monitoring and management

NMB will be monitored by acceleromyography at the adductor pollicis muscle using TOF-watch-SX™ (Organon, Oss, Netherlands) [40]. The arm without the IV cannula will be abducted and stabilized on an arm board. The thumb will be fixed to a flexible adaptor that will provide a constant preload. The other four fingers will be secured to minimize movement during nerve stimulation. After degreasing and cleansing of the skin with alcohol, two stimulating electrodes will be attached over the ulnar nerve, with the negative electrode on the wrist and the positive electrode placed 3–6 cm proximally. A transducer will be placed at the tip of the adductor pollicis. After the eyelash reflex disappears but before the administration of rocuronium, the TOF-watch-SX™ will be calibrated via the following steps. (1) A maximal response will be obtained using single-twitch stimulation (1 Hz for 0.2 ms) by gradually increasing the electrical current from 10 mA. (2) A supramaximal response will be triggered by an electrical current 15% above that necessary for a maximal response. (3) The TOF pattern (a set of four supramaximal stimuli at 2 Hz for 0.2 ms) will be applied to test the stability of the baseline response (variation in the TOF ratio < 5%) for 3 min. If the baseline response is not stable, the device will be recalibrated. Mask ventilation will be performed during calibration.

After successful calibration, 0.6 mg/kg rocuronium will be administered in the two moderate-NMB groups (S + M group and L + M group) and 1 mg/kg in the two deep-NMB groups (S + D group and L + D group). The TOF ratio will be measured every 1 min during anesthesia. When there is no response to TOF, the PTC pattern will be applied every 5 min, which is a single-twitch stimulation (2 Hz for 0.2 ms) starting 3 s after a tetanic stimulus (50 Hz for 5 s). In the two moderate-NMB groups, rocuronium will be continuously infused at an initial rate of 0.3 mg/kg/h, and the rate will be adjusted to maintain a TOF of 1–2. In the two deep-NMB groups, the infusion rate will be 0.6 mg/kg/h at first and then titrated for a targeted PTC of 1–2. Rocuronium infusion will be discontinued when pneumoperitoneum deflates.

Rocuronium (10 mg/ml) will be diluted by the nurse aware of the allocation. The concentration used at induction will be 0.1 × body weight (Wt) mg/ml in the deep-NMB groups and 0.06 × Wt mg/ml in the moderate-NMB groups; thus, 10 ml will be given in all four groups. The concentrations used for continuous infusion in the deep-NMB and moderate-NMB groups will be 0.06 × Wt mg/ml and 0.03 × Wt mg/ml, respectively; thus, the initial rate should be 10 ml/h. Therefore, one cannot tell the grouping from the injection dose or pump rate. An opaque curtain will be used to cover the NMB monitor. Only the nurse will be allowed to access the monitor and see the screen. If the NMB depth deviates from the target, the nurse will ask the anesthesiologist to adjust the pump rate.

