### Participant selection

All patients scheduled for elective laparoscopic pelvic surgeries under general anesthesia will be screened for eligibility by an investigator who will not be involved in the process of randomization, intervention, data collection, or outcome assessment. Patients will be considered eligible if they meet the inclusion criteria and do not meet the exclusion criteria. Written informed consent will be obtained after evaluation.

The inclusion criteria are as follows:
Age 18–70 yearsAmerican Society of Anesthesiologist (ASA) Classification II-IIIDiagnosis of diabetes mellitusEstimated surgery duration > 3 h. The estimated surgery duration will be determined by the average duration of the same type of surgery by the same surgeon in the last year.

The exclusion criteria are as follows:
Not willing to participate in the study or unable to sign informed consentDiagnosis of any kidney diseases other than diabetic kidney diseasesSevere renal insufficiency defined as serum Cr > 2 times the upper limit of normal, urine output < 0.5 ml/kg/h, or estimated glomerular filtration rate (eGFR) < 60 ml/hSevere liver, lung or heart dysfunctionKnown or suspected neuromuscular diseaseUse of drugs that may affect neuromuscular block monitoringSevere diabetic neuropathy or any other peripheral neuropathyKnown or suspected allergy to general anestheticsFamily history of malignant hyperthermiaPrevious history of pelvic surgery

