### Randomization and blinding

After enrollment, just prior to the surgery, the patients will be randomized by a statistician without the knowledge of random allocation in a balanced manner to one of the four groups. The allocation sequence will be computer-generated using random block sizes and will be kept in an opaque sealed envelope. These assignment envelopes will only be opened by a nurse, who will set the pneumoperitoneum pressure, prepare the muscle relaxant, and monitor the depth of NMB. Therefore, participants, anesthesiologists, surgeons, and outcome assessors will all be blinded to the allocation throughout the trial.

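### Above 100 kg, the deep-block induction syringe cannot be diluted from 10 mg/ml rocuronium, so the 1 mg/kg dose and the equal 10 ml volume cannot both hold

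*Protocol article*

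**What the plan says.** All of the following is in the protocol article.

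- **Dose.** Under Neuromuscular block monitoring and management, the induction dose of rocuronium is 0.6 mg/kg in the two moderate-NMB groups and "1 mg/kg in the two deep-NMB groups".
- **Preparation.** The same section starts from a fixed stock: "Rocuronium (10 mg/ml) will be diluted by the nurse aware of the allocation". For the deep arms, "The concentration used at induction will be 0.1 × body weight (Wt) mg/ml in the deep-NMB groups"; for the moderate arms, "0.06 × Wt mg/ml in the moderate-NMB groups; thus, 10 ml will be given in all four groups".
- **Conclusion drawn.** From the equal volume and the equal initial pump rate the section infers: "Therefore, one cannot tell the grouping from the injection dose or pump rate".
- **Blinding.** Randomization and blinding states that "participants, anesthesiologists, surgeons, and outcome assessors will all be blinded to the allocation throughout the trial".
- **Eligibility.** Participant selection says "Patients will be considered eligible if they meet the inclusion criteria and do not meet the exclusion criteria". Neither list contains a weight or body-mass-index limit. The article gives no dose cap, no ideal-body-weight rule, no stronger stock and no alternative volume for heavy patients.

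**The concern.** A diluted solution cannot be stronger than the stock it came from. The deep-arm induction concentration rises in proportion to body weight, so at some weight it passes 10 mg/ml and the syringe can no longer be made. Beyond that weight the nurse has to break one of two stated rules: inject more than 10 ml, or give less than 1 mg/kg.

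The first choice undermines the blinding device, because over a wide weight range a volume above 10 ml would occur only in a deep arm. The anesthesiologist, who is meant to be blinded and who adjusts the rocuronium pump, could then infer the NMB allocation. The second choice keeps the blind but gives a starting dose below protocol in one arm only.

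**Working it through.** **Inputs** (Neuromuscular block monitoring and management, unless stated): stock 10 mg/ml; induction doses 1 mg/kg (deep) and 0.6 mg/kg (moderate); induction concentrations 0.1 × Wt and 0.06 × Wt mg/ml; infusion starting rates 0.6 and 0.3 mg/kg/h; infusion concentrations 0.06 × Wt and 0.03 × Wt mg/ml; 162 patients per group (Sample size calculation and statistical analysis).

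**Step 1: reproduce the stated volumes.** Volume = dose × Wt ÷ concentration, and Wt cancels.

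- Induction: deep 1/0.1 = 10 ml; moderate 0.6/0.06 = 10 ml.
- Infusion: deep 0.6/0.06 = 10 ml/h; moderate 0.3/0.03 = 10 ml/h.

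The algebra is right wherever the syringe can be made.

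**Step 2: find where it can be made.** With concentration k × Wt, the condition k × Wt ≤ 10 gives Wt ≤ 10/k.

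| Syringe | k | Largest weight |
|---|---|---|
| Induction, deep | 0.1 | 100 kg |
| Induction, moderate | 0.06 | 166.7 kg |
| Infusion, deep | 0.06 | 166.7 kg |
| Infusion, moderate | 0.03 | 333.3 kg |

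Only the deep induction syringe fails at a weight likely to be met.

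**Step 3: consequence per patient.** Ten millilitres of undiluted stock holds 10 × 10 = 100 mg.

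| Weight | Deep: concentration required | Volume if 1 mg/kg is kept | Dose if 10 ml is kept | Moderate: concentration in 10 ml |
|---|---|---|---|---|
| 100 kg | 10 mg/ml | 10 ml | 1.00 mg/kg | 6.0 mg/ml |
| 110 kg | 11 mg/ml | 11 ml | 100/110 = 0.91 mg/kg | 6.6 mg/ml |
| 120 kg | 12 mg/ml | 12 ml | 100/120 = 0.83 mg/kg | 7.2 mg/ml |

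**Step 4: how many patients.** The article gives no weight distribution, so the following are assumptions. The deep arms hold 2 × 162 = 324 patients. If weight is normal, the expected number above 100 kg is 324 × P(Wt > 100).

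| Assumed mean/SD (kg) | Share above 100 kg | Expected of 324 |
|---|---|---|
| 65/11 | 0.07% | 0.24 |
| 70/12 | 0.62% | 2.0 |
| 75/15 | 4.8% | 15.5 |
| 80/16 | 10.6% | 34.2 |

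**The case against.** The strongest reply is that nothing stated is miscalculated: the scheme is consistent and works for every patient up to 100 kg. What remains is an edge case in drug preparation, of a kind that a full protocol or a preparation sheet might settle. The number affected rests wholly on assumption, and at the low end nobody is affected.

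The harm is also bounded. If the nurse keeps 10 ml, the blind holds and the dose at 120 kg, 0.83 mg/kg, is still well above the moderate 0.6 mg/kg. Deep block is defined by a post-tetanic count of 1–2, not by the bolus, and the infusion is titrated to that target. If the nurse gives more, only the NMB factor can be revealed, and to someone who does not rate the outcomes: surgeons score the field and laboratory staff analyse cystatin C. Stated targets for hemodynamics, fluids and bispectral index further limit what an unblinded anesthesiologist could change.

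Most of this stands, and it limits the severity. The argument from omitted detail does not. The article itself states the stock, the formula, the volume and an unqualified blinding conclusion, and these cannot all be true over part of the eligible weight range. One route to bias also stays open, though the article gives no basis for sizing it: bucking or body movement is a secondary outcome that anesthetic management could influence.

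**Conclusion.** The point holds, at minor severity. For any deep-NMB patient above 100 kg, the 10 ml volume and the 1 mg/kg dose are incompatible with 10 mg/ml stock. This is exact and assumes only that the stated stock and total body weight are used, as written. Between 100 and 166.7 kg the failure is confined to the deep arms, so a volume above 10 ml there would point to deep block.

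The effect is limited to the induction bolus and to blinding of the NMB factor. Target depth is still reached by titration, and neither the pressure allocation nor the cystatin C measurement is exposed. How many patients are affected is unknown and probably small.

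**What to change.** Replace the 10 ml induction syringe with a 20 ml syringe in all four groups, at 0.05 × Wt mg/ml (deep) and 0.03 × Wt mg/ml (moderate). The doses are unchanged: 20 × 0.05 = 1 mg/kg and 20 × 0.03 = 0.6 mg/kg. The preparation limits become 10/0.05 = 200 kg and 10/0.03 = 333.3 kg.

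A more proportionate alternative is to keep 10 ml up to 100 kg and use the 20 ml syringe for every patient above 100 kg in every arm, so that the volume depends on weight and never on allocation. The infusion scheme needs no change up to 166.7 kg.

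The cost is one sentence in the section on neuromuscular block management and a line on the nurse's preparation sheet. Doses, sample size and analysis stay as they are. The drawback is a larger injected volume, 20 ml instead of 10 ml, for everyone or only for the heavier patients.

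### The masking described for depth of neuromuscular block hides the monitor but not the stimulated hand, whose movement at target depth differs between the deep and moderate arms

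*Protocol article*

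**What the plan says.** The blinding claim is in the Protocol article under Randomization and blinding: "Therefore, participants, anesthesiologists, surgeons, and outcome assessors will all be blinded to the allocation throughout the trial". One nurse opens the envelope, prepares the relaxant and watches the block.

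The masking of NMB depth is set out under Neuromuscular block monitoring and management. Rocuronium is diluted by body weight so that bolus volume and starting pump rate are the same in all groups. The display is then hidden: "An opaque curtain will be used to cover the NMB monitor". Access to it is limited to the unblinded nurse.

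The same section describes the set-up at the hand: "The arm without the IV cannula will be abducted and stabilized on an arm board". The fingers are restrained, while the thumb is held in an elastic mount against which it can move.

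TOF stimulation is given once a minute. The post-tetanic count (PTC) is conditional on the TOF result: "When there is no response to TOF, the PTC pattern will be applied every 5 min".

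Study design sets the targets: a TOF count of 1–2 for moderate block and a PTC of 1–2 for deep block. The article mentions no cover, drape or screen for the arm or hand.

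**The concern.** The curtain hides a readout of a signal that the hand itself gives. If a member of the room staff can see the thumb, covering the screen does not keep the NMB arm from them.

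Three groups matter:
- **The operating surgeon** scores the Leiden scale live every 15 min (Surgical condition rating). Table 2 words the scale around contractions, movements and the need for more blocking agent, so a belief about block depth can feed directly into the score.
- **The two data collectors** record outcomes during surgery (Data collection), including bucking or body movement. No separate video assessment is described for that outcome.
- **The anesthesiologist** changes the rocuronium pump rate at the nurse's request, and anesthesia care also covers propofol, remifentanil, blood pressure and fluids. Knowledge of the arm could lead to different co-management.

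The Background makes it an objective to find out whether deep NMB improves surgical conditions. The live rating and the movement record are among the outcomes that answer it. Expectation bias would probably favor deep block, which is the direction of the hypothesis.

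**Working it through.** **1. What the dilution scheme achieves.** With body weight Wt in kg, and concentrations and volumes from Neuromuscular block monitoring and management:
- Deep bolus: 0.1 × Wt mg/ml × 10 ml = 1.0 × Wt mg, or 1.0 mg/kg.
- Moderate bolus: 0.06 × Wt × 10 = 0.6 × Wt mg, or 0.6 mg/kg.
- Deep infusion: 0.06 × Wt mg/ml × 10 ml/h = 0.6 mg/kg/h.
- Moderate infusion: 0.03 × Wt × 10 = 0.3 mg/kg/h.

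All four match the stated doses at any weight. The scheme works for bolus volume and starting rate, so that part of the masking is sound.

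**2. What the thumb does at target depth.** This follows from the definitions in Study design and the schedule in the NMB section.

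| | Moderate (TOF 1–2) | Deep (PTC 1–2) |
|---|---|---|
| Response to TOF, every 1 min | 1–2 twitches | none |
| Post-tetanic sequence, every 5 min | not triggered, since TOF responds | 1–2 twitches after a 5-s tetanus |

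**3. How often the difference appears.** Take 180 min at target as an illustration, because the inclusion criteria require an estimated surgery duration above 3 h:
- TOF trains: 180 / 1 = 180.
- Moderate arm: 180 × 1 = 180 to 180 × 2 = 360 twitches to TOF.
- Deep arm: 0 twitches to TOF. Post-tetanic sequences: 180 / 5 = 36, giving 36 × 1 = 36 to 36 × 2 = 72 twitches.

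These counts hold only while the patient is at target. Any patient with no TOF response gets the PTC pattern, so a moderate-arm patient soon after the bolus could look like a deep-arm patient.

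**4. Measures set against cues.**

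| Cue to NMB depth | Measure described |
|---|---|
| Bolus volume | Equal by dilution |
| Starting pump rate | Equal by dilution |
| Monitor display | Curtain, nurse-only access |
| Thumb movement | None described |

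**5. Which outcomes the gap reaches.**
- Exposed if the hand is seen: the live Leiden rating, the bucking or movement record, and anesthetic co-management.
- Not exposed: cystatin C and creatinine are measured by hospital laboratory staff. Four of the five surgeons rate from endoscopic video, which does not show the hand.
- The cue carries no information on pneumoperitoneum pressure, because the two factors are allocated in a 2 × 2 design.

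**The case against.** The strongest reply is that the article never says the hand can be seen. It places the arm on a board and is silent on whether surgical drapes, a warming cover or an anesthesia screen lies over it. A journal article condenses the full protocol, and draping is the kind of detail it may leave out. This stands in part, and it limits the wording of the point. It does not remove it, because the article does not leave NMB masking to another document. It gives dilution factors, the monitor curtain and, for pressure, opaque tape on the screens. Followed as written, those steps leave thumb movement unaddressed, and incidental cover by a drape is not a blinding procedure.

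A reader might infer more than the text supports:
- *That the hand stays in view and the blind cannot hold.* Visibility is not stated. The text shows only that the described measures do not protect against it.
- *That the depths are defined by visible movement.* They are defined by TOF and PTC counts and measured with a transducer. How reliably one or two weak twitches can be read by eye is not established.
- *That a short look always separates the arms.* The contrast applies at target depth, and the article itself expects deviations from target.
- *That all 648 patients are affected.* Bias needs someone to see the hand, draw the inference and act on it. All 648 are managed under the same described measures, which is a weaker statement.

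Three further points for the plan stand. Duration of surgery is also a surgical-condition outcome and is not a subjective rating. Co-management is constrained by targets for bispectral index, blood pressure, heart rate and stroke volume variation. Depth-driven pump changes are initiated by the nurse.

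**Conclusion.** The point holds in a limited form. The measures described for NMB depth conceal volume, starting rate and display, but not the thumb response, which at target depth differs systematically between the arms. An anesthesiologist, operating surgeon or in-room data collector who can see the hand could therefore infer NMB depth, and the blinding statement is not secured for them.

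The size of any bias cannot be calculated from the document. Its reach can be stated: one of the five surgical-condition raters, the bucking or movement record, and co-management by the anesthesiologist. Measurement of the primary outcome and the four video ratings stay masked.

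The conclusion assumes that the listed measures are the ones to be used, that patients are at target depth for an appreciable part of the operation, and that at least one of these staff can see the hand. If the full protocol already screens the arm, one sentence saying so settles the matter.

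**What to change.** Under Neuromuscular block monitoring and management, extend the opaque covering from the monitor to the stimulated forearm and hand. Use a tent or arm-board screen that leaves the thumb free to move and is open only to the unblinded nurse. Put it in place before rocuronium is given and keep it until the last intraoperative outcome has been recorded. If this is not practicable, narrow the statement under Randomization and blinding to those whose masking is actually secured.

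In either case, report the surgical-condition result from the four video ratings alone as a supporting analysis. Those ratings are already collected, so this needs no new data.

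The cost is one drape or screen per case and a sentence or two of text. No extra staff are needed, and doses, depth targets and sample size do not change. The small downside is that the nurse must check the transducer position under the screen.

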#### Pneumoperitoneum pressure management

The nurse aware of the allocation will be the first to enter the operating room. She will initially set the pneumoperitoneum pressure at 7 mmHg in the LPP group and 12 mmHg in the SPP group. The pneumoperitoneum pressure can be increased to a maximum of 10 mmHg in the LPP group and 15 mmHg in the SPP group, if the surgery cannot proceed due to poor surgical sight. All the screens displaying intra-abdominal pressure will be covered with opaque tape; thus, the patients, surgeons, and data collectors will be blinded. The pneumoperitoneum pressure will remain unchanged during surgery.

#### Surgical condition rating

A well-validated, 5-point scale, Leiden’s surgical condition rating scale (Table 2) [33], will be used. The laparoscopic pelvic surgeries for the enrolled patients will be performed by five surgeons. Before the study begins, they will be asked to watch the videos demonstrating examples of scales 1–5.

**Table 2 Tab2:** The surgical rating score [33]

Score	Impression	Description
1	Extremely poor conditions	The surgeon is unable to work because of coughing or because of the inability to obtain a visible laparoscopic field because of inadequate muscle relaxation. Additional neuromuscular blocking agents must be given.
2	Poor conditions	There is a visible laparoscopic field, but the surgeon is severely hampered by inadequate muscle relaxation with continuous muscle contractions, movements, or both with the hazard of tissue damage. Additional neuromuscular blocking agents must be given.
3	Acceptable conditions	There is a wide visible laparoscopic field but muscle contractions, movements, or both occur regularly causing some interference with the surgeon’s work. There is the need for additional neuromuscular blocking agents to prevent deterioration.
4	Good conditions	There is a wide laparoscopic working field with sporadic muscle contractions, movements, or both. There is no immediate need for additional neuromuscular blocking agents unless there is the fear of deterioration.
5	Optimal conditions	There is a wide visible laparoscopic working field without any movement or contractions. There is no need for additional neuromuscular blocking agents.

During the surgery, the surgeon will evaluate with the scale every 15 min starting from the introduction of the first trocar. At the same time, a 1-min video will be recorded by a camera connected to the endoscopic probe. The other four surgeons who will not perform this surgery will evaluate by watching videos independently. If the surgical condition suddenly worsens, additional assessments will be performed.

#### Postoperative management

Patients will stay in the postanesthesia care unit for 15–20 min and then return to the surgical ward, where they will spend at least 3 days before discharge. Nephrotoxic medications will be avoided in the postoperative period.

### Outcome measures

The primary outcome is serum CysC level, which is a sensitive biomarker of renal injury, and this will be measured 30 min before pneumoperitoneum insufflation (T1), 30 min after pneumoperitoneum deflation (T2), 24 h postoperatively (T3), and 72 h postoperatively (T4). Among them, T1 will be the baseline. The mean difference of the serum CysC between groups will be used as the effect measure. We will compare the serum CysC between groups throughout T2, T3, and T4, using mixed-effect model which can provide an estimate for the overall effect in the whole timeframe.

The secondary outcomes include four indicators of renal function: (1) serum Cr level measured at T1, T2, T3, and T4; (2) intraoperative urine output; (3) the presence of erythrocytes in urinary sediment on postoperative days 1 and 3; and (4) renal tissue oxygen saturation measured every 15 min following pneumoperitoneum insufflation, and cerebral oxygen saturation will be used as an internal reference to adjust individualized differences. The other three secondary outcomes selected to evaluate surgical conditions are (1) surgical condition rating scale measured every 15 min starting from the introduction of the first trocar by five surgeons independently, (2) duration of surgery, and (3) the occurrence of bucking or body movement during the surgery. The details of the secondary outcomes are demonstrated in Table 3.

**Table 3 Tab3:** The secondary outcomes

Domain	Measurement	Metric	Aggregation	Time point
renal function	serum Cr level	difference between groups in the whole timeframe	mean	30 min before PP insufflation, 30 min after PP deflation, postoperative 24 h, and postoperative 72 h
renal function	intraoperative urine output	difference between groups	mean	NA
renal function	the presence of erythrocytes in urinary sediment	difference between groups	portion	postoperative day 1 and day 3
renal function	renal tissue oxygen saturation	difference between groups in the whole timeframe	mean	every 15 min since PP insufflation
surgical condition	surgical condition rating scale	difference between groups in the whole timeframe	median	every 15 min starting from the introduction of the first trocar
surgical condition	duration of surgery	difference between groups	mean	NA
surgical condition	the occurrence of bucking or body movement during surgery	difference between groups	portion	NA

*Abbreviations*: *NA* not applicable, *PP* pneumoperitoneum

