### Interventions

#### Anesthesia

An intravenous (IV) cannula will be inserted for the administration of anesthetic drugs. All enrolled patients will receive total intravenous anesthesia (TIVA). Intraoperative monitoring will include electrocardiography (ECG), pulse oximetry (SpO_2_), invasive arterial blood pressure (ABP), stroke volume (SV) and stroke volume variation (SVV) measured by LiDCO-rapid™, inspiratory and expiratory gas analysis, pressure of end tidal carbon dioxide (PetCO_2_), tidal volume, airway pressure, bispectral index (BIS), cerebral oxygen saturation, renal tissue oxygen saturation, nasopharyngeal temperature, and peripheral skin temperature. Anesthesia will be induced via the target-controlled infusion (TCI) of propofol (at an effect-site concentration of 6 μg/ml) and a bolus injection of 2–3 μg/kg fentanyl or 0.2–0.3 μg/kg sufentanil. Endotracheal intubation will be performed after the administration of a predefined dose of rocuronium based on the grouping. Anesthesia will be maintained with a TCI of propofol and continuous infusion of remifentanil. Mean blood pressure and heart rate fluctuations will be maintained within 20% of baseline, and the targeted BIS value will be 50–60. Fluid infusion will be adjusted to maintain SV < 10% and SVV < 13. Patients will be mechanically ventilated using a volume-controlled pattern with a tidal volume of 7–9 ml/kg and a frequency of 10–13/min. PetCO_2_ will be maintained between 35 and 45 mmHg. Forced-air warming will be used to maintain central and peripheral skin temperatures ≥ 36 °C and 32 °C, respectively.

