### Sample size calculation and statistical analysis

A previous study [15] reported that the standard deviation of serum CysC level after laparoscopic procedures is 0.738 ± 0.186 mg/dl. For a CysC difference of 0.05 mg/dl to be considered clinically significant, a power analysis program (G* power 3.1) calculated that a total sample size of 582 patients is needed to achieve 90% power at the 5% significance level. Considering a 10% dropout rate, a total of 648 patients (162 per group) is necessary. Approximately 5000 patients are scheduled for elective major pelvic surgery in PUMCH every year, and approximately 15% of them have diabetes; thus, one year is estimated as necessary to achieve adequate participant enrollment.

We will first compare the two SPP groups with the two LPP groups and then compare the two deep-NMB groups with the two moderate-NMB groups. Finally, all four groups will be compared.

The baseline characteristics and intraoperative factors of the enrolled patients will be evaluated using descriptive analysis. Continuous variables will be summarized as the mean  ±  standard deviation (SD) or median (interquartile range, IQR) as appropriate, whereas categorial variables will be summarized as the number (percentage). The baseline characteristics will be compared between groups using the standardized difference, and a standardized difference < 0.2 will be considered an acceptable balance between groups. Unbalanced variables at baseline will be included in the ANOVA or mixed-effects model to adjust for the potential confounding effect.

Considering the multiple measures of CysC, Cr, surgical condition rating scale, and renal tissue oxygen saturation at different time points, the effect of intervention in the whole timeframe will be analyzed by a mixed-effects model. Other continuous variables will be compared by two-sided independent Student’s t tests or the Mann–Whitney U test, as appropriate. Categorical variables will be analyzed by a Chi-square test or Fisher’s exact test, as appropriate. The Bonferroni method will be used to correct the potential increase in the probability of a type I error when analyzing the differences between the four groups.

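### Renal tissue oxygen saturation has no stated pre-insufflation reading, so this secondary outcome loses precision and cannot describe change from before the pressure rise

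*Protocol article*

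**What the plan says.** Outcome measures lists, as the fourth renal secondary outcome, "renal tissue oxygen saturation measured every 15 min following pneumoperitoneum insufflation". Table 3 gives the time point as "every 15 min since PP insufflation". Neither names a reading before insufflation.

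The two serum markers are treated differently. Creatinine is "serum Cr level measured at T1, T2, T3, and T4", where T1 is half an hour before insufflation. For cystatin C the text adds "Among them, T1 will be the baseline".

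For differences between patients in the saturation signal, the same sentence states that "cerebral oxygen saturation will be used as an internal reference to adjust individualized differences". It does not say when the cerebral value is read or how it enters the analysis.

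The section on sample size and statistical analysis names renal saturation among the repeatedly measured outcomes, for which "the effect of intervention in the whole timeframe will be analyzed by a mixed-effects model". The target is therefore a difference between randomized groups averaged over the readings.

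The Anesthesia section includes "cerebral oxygen saturation, renal tissue oxygen saturation, nasopharyngeal temperature, and peripheral skin temperature" in the intraoperative monitoring of all patients. It gives no time at which these monitors start.

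**The concern.** The Background argues that raised intra-abdominal pressure reduces renal perfusion. Renal saturation is the only listed renal outcome read repeatedly while that pressure is applied, yet its schedule begins with the exposure. The protocol recognises that patients differ in this signal. The most direct handle on those differences is the same patient's renal value before insufflation, and it is not scheduled.

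Two things are at stake. The first is precision: stable differences between patients stay in the error term unless something removes them. The second is description: the Discussion counts this measure among those expected to detect small changes in renal function, and a change from before insufflation cannot be computed without a starting value. A later analysis plan can choose a model, but it cannot adjust for a value that was not collected.

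**Working it through.** **1. Timing, side by side.**

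| Outcome | Stated pre-insufflation value | Later values |
|---|---|---|
| Cystatin C | T1, named as baseline | T2, T3, T4 |
| Creatinine | T1 | T2, T3, T4 |
| Renal saturation | none stated | every 15 min from insufflation |
| Cerebral saturation (reference) | none stated | timing not stated |

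Table 3 counts from insufflation, so a reading at time zero is conceivable. It would be a baseline only if taken before the pressure rises, and the wording does not say so.

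**2. Whether the cerebral reference fills the gap.** It may remove some variation between patients, but it measures another tissue and no pre-insufflation cerebral value is scheduled. If it is read alongside the renal values, it is taken after randomization and under the assigned pressure. Were pressure to affect it, adjusting for it could remove or distort part of the effect of interest. A renal value taken before insufflation cannot be affected by the assigned pressure.

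**3. The plan's own figure.** No SD, correlation or target difference is given for renal saturation. The only sample-size figure is for cystatin C (SD 0.186, difference 0.05, 90% power, two-sided 5%):

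n per pressure arm = 2 × [(1.960 + 1.282) × 0.186 / 0.05]² ≈ 291, or 582 in total.

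582 / 0.9 = 646.7, so 647, and 648 as a multiple of four. This agrees with the protocol and is untouched by the present point.

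**4. Illustration of what a baseline is worth.** Assumptions, none from the protocol:
- k = 12 post-insufflation readings (180 min / 15 min, suggested by the inclusion criterion of an expected duration above 3 h);
- the same correlation r between any two readings of a patient, baseline included;
- no cerebral adjustment;
- 291 patients per pressure arm.

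In units of the squared SD of a single reading:
- variance of a patient's mean, post-insufflation readings only: v = (1 + 11r) / 12;
- the same, adjusted for one baseline reading: v − r²;
- difference detectable with 90% power: (1.960 + 1.282) × √(2 × variance / 291), in SDs of a single reading.

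| r | v | v − r² | Ratio | SE ratio | Detectable, post only | Detectable, with baseline |
|---|---|---|---|---|---|---|
| 0.3 | 0.358 | 0.268 | 0.75 | 0.87 | 0.161 | 0.139 |
| 0.5 | 0.542 | 0.292 | 0.54 | 0.73 | 0.198 | 0.145 |
| 0.7 | 0.725 | 0.235 | 0.32 | 0.57 | 0.229 | 0.130 |
| 0.8 | 0.817 | 0.177 | 0.22 | 0.47 | 0.243 | 0.113 |

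The variance falls by about 25% (r = 0.3) to 78% (r = 0.8).

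The number of readings matters little. The reduction is r²/v, and v tends to r as k grows, so the reduction tends to r itself: 30% at r = 0.3 and 80% at r = 0.8. The correlation drives the result.

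**The case against.** The planned quantity is a difference between randomized groups, not a fall within a patient. Sensor site, body habitus and diabetic kidney disease are balanced in expectation, so the comparison is valid without a baseline. This stands.

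The protocol does plan an adjustment, the cerebral reference. A reader might infer that the comparison carries all the between-patient variance; the documents do not support that. The relevant gain is what a renal baseline adds beyond the cerebral reference, and that cannot be computed from the protocol. This stands too, and it makes the figures above a best case. A correlation that weakens over hours of surgery would also lower them.

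A reader might also infer that the sensor is already running before insufflation and the value is simply left unrecorded. The Anesthesia section lists the monitor without a start time. Table 1, which marks baseline variables separately, is not visible. Data collection allows information saved in monitors to correct and supplement the data, so an early value might be recovered. These points limit confidence. They do not remove the gap, because the two visible places that define the outcome name no pre-insufflation value to record or recover.

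Finally, even without a baseline the detectable difference is roughly 0.16 to 0.24 SD under the same assumptions, so this outcome is not short of power for modest effects.

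**Conclusion.** The point holds as a minor one, with moderate confidence. As timed in the text and in Table 3, renal saturation has no stated pre-insufflation baseline, unlike cystatin C and creatinine, and the cerebral reference is an imperfect substitute. What is lost is precision and the ability to describe change from before insufflation.

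It would be too strong to say that the outcome cannot show an effect of pressure or that its comparison is biased: randomization protects the between-group difference in renal saturation. The primary outcome and the sample size of 648 are unaffected.

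The size, a variance reduction of about 25% to 78%, rests on an assumed constant correlation of 0.3 to 0.8, 12 readings and no cerebral adjustment. The true gain is smaller to the extent that the cerebral reference already works.

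**What to change.** In Outcome measures and Table 3, add one renal saturation reading, with its paired cerebral reading, immediately before insufflation. Record both on the CRF, enter the renal value as baseline covariate in the mixed model for this outcome, and report change from it descriptively. If Table 1 or the full protocol already lists such a reading, it is enough to say so in Table 3 and name it as the covariate.

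One limit should be stated. A reading just before insufflation comes after the allocated rocuronium dose. It is a clean baseline for the pressure contrast but not fully for the neuromuscular block contrast. A reading taken before rocuronium would serve both.

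The cost is one CRF line per patient and one covariate, using monitors already listed for every patient. The change has to be made before recruitment, since a value not collected may not be recoverable.
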